## 12.2. The Number of Participants

The maximum number of participants available to evaluate the drug efficacy is 100. The data will be analysed sequentially and stopping rules applied.

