## 5. DRUG INFORMATION

TKM-130803 is a drug that has been developed specifically to target EBOV. TKM-130803 is a lipid nanoparticle formulation of 2 small interfering RNAs (siRNAs) directed against Ebolavirus L polymerase and Viral Protein-35 (VP-35). These two proteins are involved in transcription and replication of EBOV. TKM-130803 is a new formulation of drug TKM-100802 (formerly TKM-100201), which has been adapted to improve its specificity to the Guinea variant viral strain causing the current outbreak by a two nucleotide swap in the VP35 siRNA and a single nucleotide swap in the L-pol siRNA to ensure complete match to the emergent strain. TKM-100201 and TKM 100802 have been evaluated in guinea pig, non-human primate, and human Phase 1 clinical trials. TKM-130803 treatment of Rhesus monkeys at 72 hours following challenge with a lethal dose of Ebola virus Guinea 2014 led to 67% survival (2/3 animals). TKM-100802 drug has received authorization for emergency use in EVD patients from the US Food and Drug Administration. 100 treatment courses of TKM-130803 are available for this trial, in a wet (non-lyophilized) formulation.

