## 12. STATISTICS

## 12.1. Description of Statistical Methods

The trial is designed to determine whether TKM is a promising treatment for Ebola. No early stopping in the case of evidence of efficacy is proposed, as there are currently only 100 courses of TKM available so early general roll out of the treatment is not possible. Enrolling the full 100 patients will maximize the precision of the final estimate of efficacy.

A futility design (Whitehead and Matsushita, 2003) is therefore used to allow early stopping in the event of evidence of futility or harm. This approach will recruit up to 100 patients, but will stop if the number of successes observed so far falls below a certain threshold.

In order to avoid early stopping due to enrollment of patients with very severe, late Ebola virus disease, who may not be expected to be salvaged even by an effective antiviral therapy, the stopping rule will be calculated after exclusion of enrolled patients who die within 48 hours of admission to the ETU.

For the purposes of determining futility, the effectiveness of the treatment will be judged in terms of the probability that a patient allocated to TKM treatment will survive to D14, after excluding patients who die within 48 hours of admission to the ETU. This probability will be denoted by  $p$ . Note that  $p$  represents the true value of the probability rather than any estimate that might be found from the trial data. The value  $p = 0.55$  will be used for guidance. If  $p \leq 0.55$ , then the treatment will be regarded as 'not promising' and the trial will be terminated.

The choice of guide value for  $p$  has been made following an analysis of individual level data on patients from a Ebola Treatment Centres from this current outbreak at Gueckedou, Foya, Kailahun and Elwa 3. Data on the outcomes of 1592 patients with laboratory confirmed Ebolavirus infection from these four centres are shown in Table 3. Only data from adults have been included, and data on patients who died on the day of admission or on the following day, or else the day after that have been omitted.

**Table 3:** Estimates and 95% confidence intervals for the probability of surviving to Day 14 following admission to the treatment centre, excluding patients who die on the date of admission or on the day after or the day after that. Success is taken to be a difference between the date of death and the date of admission that is  $> 13$  days.

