### 12.3. Criteria for the Termination of the Trial

Research sites will inform the data management centre every time that a patient is allocated to TKM treatment. Fourteen days after admission, they will report to the data management centre whether that patient did, or did not, survive to D14. Every time that a D14 report is received on a patient, a point will be plotted on Figure 5. This is plot of the number of survivals (S) reported so far against the number of D14 reports received (n), after excluding from both S and n those patients allocated to TKM treatment who died within 48 hours of admission. The plot is compared with the lower red boundary shown. If the plot reaches this boundary, the trial will be stopped with the conclusion that treatment with TKM is not promising. This safety plot will ensure a rapid reaction if TKM proves to be ineffective or harmful in the short term.

If the plot continues above the boundary until the green boundary is reached, corresponding to D14 reports being received from 100 patients, then it will be concluded that TKM is a promising treatment. If the trial has to be terminated before 100 patients have received TKM and before the lower red boundary is reached, and if stopping is due to a shortage of eligible patients rather than to any safety concerns, the final dataset will be analysed. If the outcomes of patients recruited are good enough it remains possible for TKM to be found promising, even following an incomplete study. Nevertheless, every effort will be made to complete the study of 100 patients if the lower boundary is not crossed and no important safety concerns emerge.

**Figure 5.** The stopping rule for the trial

[figure not shown]

The properties of the design have been calculated exactly, based on the independent Bernoulli distributions of each patient outcome. These are shown in Table 4 and depict the specified probability of reaching the most appropriate conclusion for a range of values of  $p$ . It can be seen that the probability is declaring TKM to be promising is set at 0.025 according to this design. Recommending a treatment associated with such a low probability of survival to D14 would be considered a type I error, and the risk

of this has been set at the conventional value of 0.025. The power of correctly identifying TKM as promising when  $p = 0.70$  is 0.827.

**Table 4:** Probabilities of claiming that TKM is promising for the phase II trial of Treatment TKM

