#### 12.5. Inclusion in Analysis

It is important to note that the primary sequential analysis described uses only data from patients who were admitted more than 14 days previously. Although it may be known that some more recently recruited patients have already died, their data will not yet be used, to avoid bias due to information on death being available sooner than information on survival. Enrolled patients who die within 48 hours of admission to the ETU will be excluded from the analysis.

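### Table 4's 0.025 and 0.827 hold for 100 evaluable D14 reports, but the cap of 100 applies before 48-hour deaths are removed, and no cut is given for a smaller n

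*Supplement*

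**What the plan says.** All references are to the final protocol (v2.9) in the Supplement.

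- **Supply.** Section 5: "100 treatment courses of TKM-130803 are available for this trial". Section 12.1 repeats that "there are currently only 100 courses of TKM available".
- **Recruitment cap.** Section 12.1: "This approach will recruit up to 100 patients". Section 12.2: "The maximum number of participants available to evaluate the drug efficacy is 100".
- **Exclusion.** Section 12.3 plots survivals S against reports n "after excluding from both S and n those patients allocated to TKM treatment who died within 48 hours of admission". Section 12.5 repeats it for the analysis set: "Enrolled patients who die within 48 hours of admission to the ETU will be excluded from the analysis".
- **Endpoint.** In 12.3 the promising conclusion follows when the plot reaches the green boundary, "corresponding to D14 reports being received from 100 patients".
- **Operating characteristics.** Section 12.3 and Table 4 give a type I error of 0.025 at p = 0.55 and power of 0.827 at p = 0.70.
- **Shortfall.** Section 12.3 covers stopping before 100 patients have had the drug because too few eligible patients are found: "If the outcomes of patients recruited are good enough it remains possible for TKM to be found promising". Section 12.4 adds an underrunning analysis, allowing for the futility rule, if the trial is abandoned for lack of patients or for another reason unrelated to its emerging results.

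**The concern.** The same figure of 100 is used for two different counts. As a cap on courses and recruited patients it applies before exclusions. As the end of the plot it applies after them. Each allocated patient who takes up a place and dies within 48 hours of admission leaves n one short of the endpoint on which Table 4 rests, and nothing inflates the 100 to allow for this.

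The plan expects such deaths: 12.1 introduces the exclusion because some enrolled patients will have very severe, late disease. They can follow allocation, since 8.1 allows consent up to 48 hours after arrival.

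Two things are at stake. The stated power belongs to an n that the trial is unlikely to reach. And if all 100 places are used with the plot above the red line but n below 100, the protocol does not say which results lead to the primary conclusion of promising.

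**Working it through.** **Inputs.** From the documents: p = 0.55 (threshold) and 0.70 (alternative); independent Bernoulli outcomes, exact calculation (12.3); a run of deaths first stops the trial at 8 patients (12.7); the nine probabilities of Table 4. Not in the documents: the share d of allocated patients excluded as 48-hour deaths, which is assumed below, and the boundary itself, because Figure 5 is not shown.

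**Step 1: reproduce Table 4.** I took a straight lower boundary checked after every report, stopping when S ≤ a + bn, and searched a and b subject to the 8-deaths condition. The best line is S ≤ −4.887 + 0.6825n.

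- n = 7: −4.887 + 4.7775 = −0.11, so no stop. n = 8: −4.887 + 5.46 = 0.57, so S = 0 stops.
- n = 100: −4.887 + 68.25 = 63.36, so 63 or fewer stops and 64 or more is promising.

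| p | Table 4 | Exact recursion to n = 100 |
|---|---|---|
| 0.50 | 0.002 | 0.0017 |
| 0.55 | 0.025 | 0.0249 |
| 0.60 | 0.158 | 0.1585 |
| 0.65 | 0.487 | 0.4868 |
| 0.70 | 0.827 | 0.8275 |
| 0.75 | 0.973 | 0.9727 |
| 0.80 | 0.998 | 0.9979 |

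All agree within 0.0005. A fixed-sample binomial test at n = 100 does not match: a cut of 65 gives 0.0272 and 0.884, and a cut of 66 gives 0.0166 and 0.837. Table 4 is thus reproduced with 100 evaluable reports and no allowance for exclusions.

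**Step 2: chance that n reaches 100.** With 100 allocated and no replacement, and leaving futility stopping aside, this is (1 − d)^100.

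| Assumed d | Chance n = 100 | Allocations needed, 100/(1 − d) |
|---|---|---|
| 0.5% | 0.61 | 101 |
| 1% | 0.37 | 102 |
| 2% | 0.13 | 103 |
| 5% | 0.006 | 106 |
| 10% | below 0.0001 | 112 |

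**Step 3: operating characteristics at a smaller n.** The same line is run to n = 95, 90 and 85. Reading A calls any plot still above the line promising. Reading B raises the final cut until the exact type I error is at most 0.025.

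| n | A: cut | A: type I error | B: cut | B: type I error | B: power at 0.70 |
|---|---|---|---|---|---|
| 100 | 64 | 0.0249 | 64 | 0.0249 | 0.8275 |
| 95 | 60 | 0.0316 | 62 | 0.0214 | 0.8124 |
| 90 | 57 | 0.0387 | 59 | 0.0228 | 0.8063 |
| 85 | 54 | 0.0460 | 56 | 0.0240 | 0.7961 |

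The A cuts follow from the line: at n = 90, −4.887 + 61.425 = 56.54, so 57 is the first value above it. The readings disagree on 60 or 61 survivors of 95, 57 or 58 of 90, and 54 or 55 of 85. For those results the protocol leaves the conclusion open.

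Letting n vary binomially under reading B gives power of 0.821 at d = 1%, 0.817 at 2%, 0.811 at 5% and 0.796 at 10%. A slightly different fitted line (S ≤ 0.6825n − 4.9) moves the fixed-n powers by about 0.001.

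**The case against.** The strongest answer is 12.4. Running out of drug fits naturally under a reason unrelated to the emerging results. Since p is defined among patients who survive 48 hours, early deaths enter neither S nor n. An estimate and 95% interval allowing for the futility rule are therefore already planned. This stands, and it removes most of the analytical worry. But 12.4 supplies an interval, not a decision rule. Section 12.3 says only that outcomes must be good enough, and it ties that route to a shortage of eligible patients.

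A reader might infer that n cannot reach 100. The documents do not support that. It happens if nobody is excluded. Courses and reports are also not one to one: allocated but untreated 48-hour survivors stay in n (7.5), and a patient who cannot be treated may be replaced the same day (7.4). A patient who dies before dosing uses no course, although the cap on recruited patients still applies.

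A reader might also infer that the trial's type I error exceeds 0.025. The documents do not support that either. The automatic promising conclusion belongs only to 100 reports, and for a shorter dataset the protocol says the data will be analysed. Reading A is one that the wording fails to exclude, not a rule the plan states.

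Finally, the exclusion rate may be low. Patients for end-of-life care only are ineligible, and some early deaths precede allocation. The interval width in Table 3 implies about 1,410 patients analysed, 0.543 × 0.457 × (1.96/0.026)², against 1,592 named, a gap of about 11%. That concerns unselected historical patients and an exclusion counted in calendar days, so it is no estimate for this trial.

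**Conclusion.** The concern holds in a limited form. The stated 0.025 and 0.827 are properties of 100 evaluable reports, while the cap of 100 applies before the exclusions, so n will probably end below 100 unless 48-hour deaths among allocated patients are very rare. With the error held at or below 0.025, power at p = 0.70 is about 0.81 at n = 95 or 90 and 0.80 at n = 85, a loss of roughly 1.5 to 3 percentage points. That is modest. The missing cut matters more, because it bears on the primary conclusion: treating any plot above the red line as promising would give a type I error of about 0.032, 0.039 and 0.046 at those n.

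The result rests on assumed exclusion rates and on a boundary inferred from Table 4. The exact cuts should be recomputed from the boundary in Figure 5.

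**What to change.** 1. In 12.3 and Table 4, say that 100 means evaluable D14 reports, after removal of 48-hour deaths.
2. State the assumed exclusion rate, and restate Table 4 and the power sentence for a plausible range of evaluable n, for example 85 to 99.
3. In 12.3 and 12.4, state that if the 100 courses or recruitment places are used with n below 100 and the red line not reached, the underrunning analysis of 12.4 applies, and TKM is declared promising only if the lower limit of that 95% interval exceeds 0.55. On the inferred boundary this means about 62 of 95, 59 of 90 or 56 of 85 survivors.

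The cost is a rerun of the exact calculation, a wording change and a slightly lower stated power. No extra patients or drug are needed.

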### 12.3. Criteria for the Termination of the Trial

Research sites will inform the data management centre every time that a patient is allocated to TKM treatment. Fourteen days after admission, they will report to the data management centre whether that patient did, or did not, survive to D14. Every time that a D14 report is received on a patient, a point will be plotted on Figure 5. This is plot of the number of survivals (S) reported so far against the number of D14 reports received (n), after excluding from both S and n those patients allocated to TKM treatment who died within 48 hours of admission. The plot is compared with the lower red boundary shown. If the plot reaches this boundary, the trial will be stopped with the conclusion that treatment with TKM is not promising. This safety plot will ensure a rapid reaction if TKM proves to be ineffective or harmful in the short term.

If the plot continues above the boundary until the green boundary is reached, corresponding to D14 reports being received from 100 patients, then it will be concluded that TKM is a promising treatment. If the trial has to be terminated before 100 patients have received TKM and before the lower red boundary is reached, and if stopping is due to a shortage of eligible patients rather than to any safety concerns, the final dataset will be analysed. If the outcomes of patients recruited are good enough it remains possible for TKM to be found promising, even following an incomplete study. Nevertheless, every effort will be made to complete the study of 100 patients if the lower boundary is not crossed and no important safety concerns emerge.

**Figure 5.** The stopping rule for the trial

[figure not shown]

The properties of the design have been calculated exactly, based on the independent Bernoulli distributions of each patient outcome. These are shown in Table 4 and depict the specified probability of reaching the most appropriate conclusion for a range of values of  $p$ . It can be seen that the probability is declaring TKM to be promising is set at 0.025 according to this design. Recommending a treatment associated with such a low probability of survival to D14 would be considered a type I error, and the risk

of this has been set at the conventional value of 0.025. The power of correctly identifying TKM as promising when  $p = 0.70$  is 0.827.

**Table 4:** Probabilities of claiming that TKM is promising for the phase II trial of Treatment TKM

| True probability of success ( $p$ ) | Probability of claiming that TKM is promising |
|-------------------------------------|-----------------------------------------------|
| 0.50                                | 0.002                                         |
| 0.55                                | 0.025                                         |
| 0.60                                | 0.158                                         |
| 0.65                                | 0.487                                         |
| 0.70                                | 0.827                                         |
| 0.75                                | 0.973                                         |
| 0.80                                | 0.998                                         |
| 0.85                                | 1.000                                         |
| 0.90                                | 1.000                                         |

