### 8.3. Follow up Assessments (D14, D30, Months 3, 6, 12)

Survival at D14 is the primary end point of this trial, and defined as survival until 23.59 on Day 14. Follow up assessments will be conducted on D14 and D30 and at 3, 6 and 12 months. Patients who have been discharged before these dates will be issued a mobile telephone for the purposes of follow-up. Patients will be invited to return to the treatment centre for the D14 and D30 visits and then subsequent follow up will occur by phone or at a treatment centre. When patients are not able or willing to attend a follow-up visit on D14 and D30 at the treatment centre, field workers will follow up by phone. Remaining follow up visits will be arranged at a survivor's clinic or suitable local health facility. An outreach team may attempt to visit participants who are unable to attend a clinic or cannot be reached by phone, if it is considered safe and feasible to do so. Reasonable expenses for travel and loss of earnings will be paid at these follow up visits.

Patient status on follow-up assessment days will be collected (admitted, met discharge criteria, deceased). In addition, visits at D30 and months 3, 6, and 12 will seek information on symptoms post recovery. Trial staff will notify appropriate healthcare providers if the patient reports new symptoms that require further clinical assessment.

Primary/secondary outcome data for these visits can be collected at any point after the respective days.

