|             | Gueckedou | Foya  | Kailahun | Elwa 3 | Overall |
|-------------|-----------|-------|----------|--------|---------|
| Lower limit | 0.485     | 0.428 | 0.514    | 0.510  | 0.517   |
| Estimate    | 0.535     | 0.495 | 0.568    | 0.554  | 0.543   |
| Upper limit | 0.585     | 0.562 | 0.622    | 0.598  | 0.569   |

As a result of this analysis,  $p = 0.55$  has been set as the success rate threshold above which TKM would be considered promising.

While children are initially excluded from the TKM arm of the trial, if the eligibility criteria is expanded to age  $>5$  following IDMC review of preliminary results, TKM trial data from adults and children will be jointly analysed, since the availability of TKM is restricted to 100 treatment courses and a stratified analysis is infeasible. Case fatality is highest in children aged  $< 5$  years, after which it declines with age reaching a minimum in persons aged about 15-20 years. Therefore the inclusion of subjects aged 5-17 years is not expected to inflate the case fatality, and the futility threshold of  $p \leq 0.55$  is expected to remain valid.

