#### 12.6. Procedure for Accounting for Missing, Unused, and Spurious Data.

While considerable effort will be made to ensure all patients are followed up at D14, D30, month 3, 6 and 12 (through return visits to clinic, phone, email or field-researcher visits), some patients may not be contactable. Leeway will have to be allowed for late reporting, but this should be limited: it may be that data on survival to D14 is not entered until Day 16 in order to avoid remaining bias due to late reporting of survival. However, if it turns out that a patient died on Day 15 or later, *then they are survivors* for the purpose of this study. If they walked away on Day 7, seemingly cured, it might be assumed that they survived to Day 14. Some judgment will necessarily be used here.

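### The futility plot takes D14 reports in order of receipt with no binding entry day, so late-traced survivors could pull it towards a wrong stop

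*Supplement*

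**What the plan says.** All references are to protocol v2.9, the latest version in the supplement.

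- Section 12.3 has sites report D14 status fourteen days after admission. "Every time that a D14 report is received on a patient, a point will be plotted on Figure 5", and reaching the lower boundary ends the trial with the conclusion that TKM is not promising.
- Table 4, in the same section, is computed exactly on the assumption of independent Bernoulli outcomes. It does not mention reporting delay.
- Section 12.5 holds back every patient until more than 14 days after admission, "to avoid bias due to information on death being available sooner than information on survival".
- Section 12.6 acknowledges that some of this bias remains: "Leeway will have to be allowed for late reporting, but this should be limited". It suggests that entry might wait until Day 16, and that a patient who left early looking well might be presumed alive at D14. It leaves both to judgment.
- Section 8.3 covers all follow-up visits: "Primary/secondary outcome data for these visits can be collected at any point after the respective days". Discharged patients are asked to return and are otherwise followed up by phone. An outreach team may try to visit those who cannot be reached.

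**The concern.** The order in which outcomes reach the plot can depend on the outcome. A death in the centre is known by D14. A patient discharged before D14 is very likely a survivor and may have to be found first. While that survivor is missing from both S and n, deaths among patients admitted later are already plotted. The sequence that meets the boundary is then no longer the one behind Table 4.

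If the trial runs to 100 reports, the final total is the same in any order. The path is not, and the stop is permanent. What is at stake is the chance of abandoning a useful drug as not promising.

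**Working it through.** **Inputs from the plan.** p = 0.55 "has been set as the success rate threshold above which TKM would be considered promising" (12.1); the risk "of this has been set at the conventional value of 0.025" (12.3); "The power of correctly identifying TKM as promising when" p = 0.70 is 0.827 (12.3); "The maximum number of participants available to evaluate the drug efficacy is 100" (12.2); and the statement in 12.7 that the trial stops after 8 patients if all die.

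**Rebuilding the boundary.** Figure 5 is not shown, so a straight line was fitted to Table 4: stop at report n if S ≤ 0.6825n − 4.898, checked after every report up to n = 100.
- At n = 7 the line is 4.778 − 4.898 = −0.12, so S = 0 does not stop.
- At n = 8 it is 5.460 − 4.898 = 0.56, so S = 0 stops, as 12.7 says.
- At n = 100 it is 68.25 − 4.898 = 63.35, so at least 64 survivors are needed.

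**Reproducing Table 4.** Let f(n, S) be the probability of being at S after n reports without having stopped. Then f(n, S) = p·f(n−1, S−1) + (1−p)·f(n−1, S), set to zero on or below the line. Summing at n = 100 gives:

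| p | Table 4 | Rebuilt |
|---|---|---|
| 0.50 | 0.002 | 0.0017 |
| 0.55 | 0.025 | 0.0249 |
| 0.60 | 0.158 | 0.1588 |
| 0.65 | 0.487 | 0.4876 |
| 0.70 | 0.827 | 0.8282 |
| 0.75 | 0.973 | 0.973 |

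The largest difference is 0.0012.

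**Why a few missing survivors matter.** At p = 0.70 the path gains on the line by only 0.70 − 0.6825 = 0.0175 per patient. Each outstanding survivor lowers the distance to the line by 1 − 0.6825 = 0.3175. The mean number outstanding in steady state is accrual × p × late share × mean delay.
- 1/day, 20% late, 7 days: 1 × 0.7 × 0.2 × 7 = 0.98 missing, a shift of 0.98 × 0.3175 = 0.31.
- 1/day, 40% late, 14 days: 1 × 0.7 × 0.4 × 14 = 3.92 missing, a shift of 3.92 × 0.3175 = 1.24.

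The starting distance is 4.898.

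**Simulated power at p = 0.70.** Admissions are random in time. Deaths are reported at 14 days. A random share of survivors is late by an exponential delay, and reports are plotted in order of receipt. Accrual, late share and delay are all assumptions. With no delay, power is 0.83.

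| Accrual/day | Survivors late | Mean delay (days) | Power |
|---|---|---|---|
| 1 | 20% | 7 | 0.81 |
| 1 | 40% | 7 | 0.78 |
| 1 | 40% | 14 | 0.73 |
| 2 | 40% | 7 | 0.73 |
| 0.33 | 40% | 7 | 0.81 |

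Over a wider grid (0.25 to 2 patients/day, 10 to 50% late), power is 0.80 to 0.83 for a mean delay of 2 days, 0.70 to 0.83 for 7 days, 0.58 to 0.82 for 14 days and 0.40 to 0.82 for 30 days. At p = 0.55 the chance of a promising claim falls from 0.025, to as low as 0.002 in the most extreme cell. The bias therefore runs towards stopping.

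**With the 12.6 guards applied.**
- Day 16 entry for everyone, at 1/day: 0.81 (20% late, 7 days), 0.80 (40%, 7 days) and 0.75 (40%, 14 days).
- In that last case, also presuming 80% of the late survivors alive gives about 0.82. Presuming all of them alive gives 0.83.
- If the Day 16 delay were applied to survivors but not to deaths, it would create the imbalance itself: 0.80 at 1/day and 0.76 at 2/day.

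**With admission-order plotting.** Power is 0.82 to 0.83 in every scenario.

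**The case against.** The strongest reply is that the plan already sees this bias and aims at it. Section 12.5 holds all data for 14 days. Section 12.6 limits leeway, suggests Day 16, and offers a presumption of survival for the very patients who are hard to trace. The discharge criteria in 9.1 (72 hours symptom-free, independent function, negative PCR) make that presumption reasonable, and survivors still in the centre at D14 need no tracing. Phones and outreach shorten delays. Accrual of 1 to 2 TKM patients a day may be high, given the daily cap in 7.2 and the staggered safety cohort in 7.4. Some operating detail may sit in the IDMC charter or the table of boundary values, neither of which is shown.

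Much of this stands. With both guards applied, even the 40%, 14-day case costs only about a point or nothing. What it does not answer is that neither guard binds, that 12.3 as written follows order of receipt, and that Day 16 entry alone still leaves 0.75 in that case.

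Two stronger readings are tempting and are not supported:
- A reader might infer that 8.3 and 12.6 set conflicting cut-offs. They do not. Section 8.3 governs when visit data may be collected, and 12.6 governs when D14 survival is entered. They are unconnected, not contradictory.
- A reader might infer that the power of 0.827 will not be delivered. That depends on accrual and tracing times the documents do not give.

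**Conclusion.** The point holds as a gap in the stopping rule. Whether Table 4 applies depends on practice that the plan leaves to judgment. If discharged survivors are traced slowly and 12.6 is not applied, power at p = 0.70 falls from 0.827 to about 0.81 in a mild case and about 0.73 in a poor one. In the poor case, wrong futility stops rise from about 17% (1 − 0.827) to about 27% (1 − 0.73). If 12.6 is applied fully, or accrual is slow and few survivors are late, the loss is about 0 to 1.5 points. Type I error is not inflated.

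These sizes rest on a boundary rebuilt from Table 4 and on assumed accrual, late share and delay. The direction of the bias requires only that late reports fall mainly on survivors. A change is worth making because the stop is irreversible and the remedy is a few sentences.

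**What to change.** In 12.3, plot patients in order of admission, with the same entry day for deaths and survivors. Declare the red boundary reached only if it would still be reached with every earlier-admitted patient whose D14 status is outstanding counted as a survivor. Counting them this way can only raise S, so any crossing declared is also a crossing in the completed sequence, and Table 4 applies again.

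In 12.6, make the rule for patients discharged before D14 binding and state it in advance. In 8.3, refer to that rule for the D14 visit.

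The cost is wording and a small change to the plotting sheet. A true futility stop may be delayed by the few days needed for tracing, and a stated tracing limit would cap that delay.
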